## Abstract

**Background:**

The problem of sedentary behavior among primary school children is alarming, with numbers gradually increasing worldwide, including Sri Lanka. Physical activity interventions within classroom settings have been acknowledged as a critical strategy to increase students’ movement behaviors while enhancing their academic achievement and health. Yet, the busy curriculum and challenging educational demands encourage more sedentary classroom behavior. Hence, this study aims to develop and evaluate an in-classroom physical activity breaks (IcPAB) intervention among fifth graders in Sri Lanka.

**Methods:**

The study will adopt a randomized controlled trial (RCT), comprising an in-classroom physical activity breaks program group and a control group to evaluate the effects of IcPAB on academic achievement, movement behaviors and health outcomes. The intervention design is based on the capability (C), opportunity (O) and motivation (M) behavior (B) (COM-B) model. A least 198 fifth graders will be recruited from two schools in Uva province, Sri Lanka. The recruitment process will start in late 2022. Class teachers of the intervention group will implement 5-min activity breaks at least three times a day after completing a training session. The primary variables include mathematics and reading achievement. The secondary variables include physical activity levels, steps count, sedentary behavior, body mass index, aerobic fitness, and perceived stress. Data collection will be implemented at pre-test and post-test, respectively. Intervention fidelity and the process will also be evaluated.

**Discussion:**

The IcPAB is designed to prevent pure educational time loss by introducing curriculum-integrated short bouts of physical active breaks into the classroom routine. If the IcPAB is effective, it can (1) improve the mathematics and reading achievement of fifth-grade girls and boys, which is a significant factor determining the performance at the Grade Five National Scholarship Examination in Sri Lanka; (2) improve movement behaviors as well as physical and mental health outcomes among primary school students. Sequentially, the IcPAB will enrich school-based physical activity intervention approaches which can in turn bring academic and health benefits to primary school children in Sri Lanka.

**Trial registration:**

The first version of the trial was registered with the ISRCTN registry (Ref: ISRCTN52180050) on 20/07/2022.

## Introduction

1

The effects of physical activity (PA) on academic achievement (1, 2), movement behaviors (3, 4) and health outcomes such as body mass index [BMI; (5, 6)], aerobic fitness (7, 8), and psychological health such as stress/ test anxiety levels (9, 10) among school children have been long established. However, reports including the elementary education sector highlighted that children should meet the recommended daily PA behavior levels, such as engaging in at least 60 min of moderate-to-vigorous physical activity [MVPA; (11)]. One primary factor influencing this figure is that children have long seated learning time in the classroom due to high academic curriculum demands in primary school (12, 13). As a result, sedentary behavior among primary school children has become alarming, with figures steadily increasing worldwide (14, 15).

A situation analysis conducted in 2016 showed that the learning time is less activity-based (16) in Sri Lanka. National surveillance data also indicated that 63 to 72% of students (age range = 6–12 years old) engaged in sedentary activities (17). Among the five grades in primary schools in Sri Lanka, the grade five curriculum is one of the most loaded and competitive in teaching and learning (18–20). The underlying reason is that grade five students are expected to sit for a national-level competitive scholarship examination in addition to their curriculum-related reviews at the term tests (18, 19, 21, 22). Therefore, the teachers and students are tense in preparing for the scholarship examination and surpassing the cutout marks while achieving the required competency levels for fifth graders (16, 19, 23, 24). This has increased the sedentary behavior with more traditional seated learning as the main objective of the teachers is to improve the students’ academic achievement. As a consequence, most of the fifth graders are identified to be physically inactive (17, 25–27), below recommended body mass index (BMI) percentiles (17, 25), aerobically unfit (18), and stressful (16, 19, 20, 23, 24, 28). Therefore, there is a need to target fifth graders in primary schools in Sri Lanka to prevent grade-related sedentary behavior and obtain health benefits and maximum academic performance.

It has been observed previously that PA breaks can improve the number of steps by 18% and minutes of MVPA by 26% during the school day (29, 30). Hence, there needs to be enablement to help manage the increased academic curriculum, and classroom settings are recommended as the best setting to achieve the benefits of PA (31–34). In the recent decade, few countries introduced the concept of in-classroom physical activity breaks (IcPAB) as a means of enhancing academic achievement (12), physical behaviors (35), and health outcomes (10, 36) by changing traditional seated learning into active learning among elementary school students. Still, more IcPAB initiatives are needed due to several limitations emphasized by a recent review based on the data from 1,538 primary school students (from 7 to 12 years old) in 10 studies (37):

(1) Not enough studies focused on introducing integrated PA into academic content through classroom-based interventions (37–40). (2) Most of those studies are introduced for populations from high-income Western countries (37, 39, 41) such as the USA, Australia, the Netherlands and Switzerland. The intervention effects based on gender are understudied. (3) Different durations were used in previous IcPAB initiatives, ranging from 10 min to 4,800 min (37), even though teachers prefer activity breaks that will take no more than 5 minutes (37), and the effectiveness of five-minute IcPAB interventions are understudied (37). (4) Previous studies demonstrated average methodological quality, with concerns around the randomization procedure, handling of missing data, outcome and process evaluation (37). This calls for future study protocols with a more robust methodological quality to avoid potential risks of bias in the IcPAB interventions, in addition to the well-explained outcome and process evaluation and fidelity methods. (5) Few studies used theoretical frameworks and evidence from related stakeholders such as teachers in designing IcPAB interventions. The review suggests (37) that robust PA interventions should be backed by well-established theories such as the capability (C), opportunity (O) and motivation (M) behavior (B) (COM-B) model (42) while considering the evidence-based opinions of the beneficiaries of the IcPAB in implementing an IcPAB program.

Therefore, there is a need for more IcPAB initiatives integrated into the curriculum across different geographic locations/ cultures (37) that require shorter bouts of time [i.e., around 5 minutes (12, 43)] with strong methodological quality (39, 44), outcome and process evaluation procedures and theoretical underpinnings (37, 39, 44). Also, the moderating effects of gender on the intervention should be further examined. Thus, by addressing the research limitations, this study aims to develop, implement, and evaluate a 12-week IcPAB program among grade five primary school children in Sri Lanka.

Depending on the aforementioned rationale, the specific research questions of this study include: (1) What is the impact of the IcPAB intervention on the primary outcome, academic achievement (mathematics and reading achievement) during the school day? (2) What is the impact of the IcPAB intervention on the secondary outcomes, movement behaviors (PA levels, steps count and sedentary behavior) and health outcomes (BMI, aerobic fitness, and perceived stress) during the school day? It is hypothesized that the IcPAB group will show improvement in all measures compared to the control group.

## Methods

2

This study received ethical approval from the Ethics Review Committee of the University of Kelaniya, Sri Lanka (Ref: UOK/ERC/SS/2022/009) and Hong Kong Baptist University (Ref: SOSC-SPEH-2022-23_113). The trial was retrospectively registered with the ISRCTN registry (Ref: ISRCTN52180050). Methods are reported by adhering to the Consolidation Standards of Reporting Trials (CONSORT) guidelines and the Standard Protocol Items: Recommendations for Interventional Trials (SPIRIT) Statement throughout the study. The completed SPIRIT Checklist is added as a Supplementary material S1.

### Study design and selection of subjects

2.1

A single-blinded parallel randomized controlled trial (RCT) will evaluate the intervention effects of IcPAB compared to a control group. Target participants will be the fifth graders in government primary schools. Based on the data shared by the Ministry of Health, Sri Lanka, the COVID-19 pandemic severity was slight in the Bandarawela Education Zone (city) in Badulla District. Therefore, the government schools of Bandarawela Education Zone were contacted to initiate the recruitment process in late 2022. The age range of the grade five students is 9 to 10 years old. The targeted population is exposed to 6 hours of regular classroom time (7.30 a.m. to 1.30 p.m.), including a 20-min lunch break according to the government primary school norms in Sri Lanka. Within the government primary school setting, the teacher in charge of a class should teach all subjects in the syllabus for the class, such as mother tongue, mathematics, religion, environment and English. Depending on the interests of the schools, the teachers will conduct additional classes after regular school time to prepare the students for the year-end national scholarship examination. Therefore, the study was designed to be implemented only during the standard classroom time for 12 weeks.

Based on GPower 3.1 software, through *a priori* power analysis, it was estimated to obtain at least 198 participants for both the intervention and control groups to expect an effect size of 0.21 [Cohen’s *f*, converted from *d*, (45, 46)] on academic achievement (mathematics) by providing a power of 0.8 (1-β) with an alpha of 0.05 to test the primary hypotheses of the study with an estimated 10% dropout rate [dropout rates were less than 10% in previous studies (10, 33, 47)] at the post-test/ follow-upstage.

Therefore, it is anticipated to recruit five to six classes (30 to 40 students per class) from two government schools to conduct the study to reach the required minimum sample size. Block randomization technique via MS Excel, will be used to randomize the sample classes by an assessor who is blinded to the intervention content and outcome assessment.

Permission was obtained first from the Bandarawela zonal education director to contact eligible government schools. For two schools to be eligible, grade five education must be offered, the students should not be exposed to similar interventions, and the principals must consent to join the research project. Once the principals grant the permission, the research team will contact the teachers in charge of the fifth-grade classes.

Teachers in charge of classes, parents/ guardians, and children at participating schools will be distributed with an informed consent form (Supplementary material S2) in plain language during the parents’ meeting days organized by the teachers. After obtaining the permissions, the principal investigator and the research assistants will visit the schools to collect data by giving prior notice to the teachers in charge of classes. The teachers will deliver the IcPAB. Therefore, all the students in the intervention classes will be exposed to IcPAB.

However, data will be collected only from the students meeting the consent requirements. The study will not include data from students with special health conditions and special education needs. An overview of the participant flow diagram (Figure 1) and the intervention schedule for enrolment and assessments [SPIRIT Figure (Figure 2)] are provided below.

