### Data analysis

2.6

Data will be statistically analyzed using IBM SPSS software version 28. A randomization check will be performed using independent t-tests (for continuous outcomes) and chi-square (for categorical variables) tests (70). Descriptive statistics such as mean, standard deviation, and percentages will be used to describe the baseline characteristics of the sample and the attrition rates. Primary analysis will be handled with an intention-to-treat modified (m-ITT) approach (71). Missing values analysis will be conducted to observe whether the data are missing completely at random (MCAR). Missing data values will be handled using the multiple imputation method with chained equations.

To test the effectiveness of the IcPAB, generalized linear mixed models (GLMM) will be used by linking to the dependent variables at the individual level (students) and group level (intervention vs. control) with time (pre to post-test) (12, 72, 73). A random intercept will be used to account for the repeated measures of the subjects (35). To test the moderation effects by gender, an interaction test will be conducted via GLMM by setting group-by-time-by-gender as the moderator (35). A 5% level (two-tailed) will be used as the statistical significance cut-off point (74). All the intervention effects will be reported based on the type III tests of fixed effects of GLMM. The estimates of the impact sizes will be written based on the estimated coefficients (*β*) with the 95% confidence intervals/ odds ratio for those estimates based on previous intervention effect report practices for IcPAB (31, 63) in addition to the mean changes in the intervention and control groups. The odds ratio (OR), where OR = 1.68, 3.47, and 6.71 are equivalent to Cohen’s *d* = 0.2 (small), 0.5 (medium), and 0.8 (large), will be used for the interpretations, respectively, (75). Furthermore, a sensitivity analysis to the m-ITT results will be facilitated by considering all the subjects who complete all the baseline and post-test measurements for all the primary and secondary outcomes to ensure the robustness of the primary data assessment and strengthen the conclusions and credibility of the study’s findings.

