### Limitations

3.1

Despite the strengths mentioned above, it is possible to indirectly affect the fidelity of the intervention due to the ongoing economic crisis and post-COVID-19 pandemic in Sri Lanka (83, 84). For example, the sudden closure of schools for a few days will reduce the number of days the IcPAB can be implemented weekly (83–85). Furthermore, participants were limited to the Uva Province in Sri Lanka. This will cause a representation bias in the data (86). The classes are randomized into intervention and control groups. This may cause potential contamination effects. Therefore, use of a cluster-RCT design is recommended to in the future studies similar to a previous study (31). There may be a potential for bias as the same teacher who is delivering the IcPAB records the fidelity of the intervention (12) even though the research team plans to conduct weekly observations of the frequency of conducting IcPAB. Also, the results may be limited by poor protocol compliance if few classes are included in the study as “one teacher could skew the results” (31).

Even though, this study was designed based on COM-B model to address the hindrances to implement classroom-based PA, effect of the factors such as participants’ dietary habits (87), challenges with school initiatives (88), children’s preferences for outdoor activities (89) will not be measured throughout the proposed RCT.

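### The 198-student sample size assumes independent students although whole classes are randomised, so the stated 80% power is unsupported and probably too high

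*Protocol article*

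**What the plan says.** Section 2.1 of the protocol article reports an a priori G*Power calculation for mathematics achievement: "it was estimated to obtain at least 198 participants for both the intervention and control groups to expect an effect size of 0.21" (Cohen's f), "by providing a power of 0.8 (1-β) with an alpha of 0.05", and "with an estimated 10% dropout rate". The Abstract also gives 198 as the recruitment figure for the whole trial, so it is the total for both arms. Section 2.6 makes the test two-sided: "A 5% level (two-tailed) will be used as the statistical significance cut-off point".

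The same section 2.1 then says that "it is anticipated to recruit five to six classes (30 to 40 students per class) from two government schools" in order to reach that minimum, and that block randomisation is applied to classes. Section 3.1 (Limitations) repeats that classes are allocated to the two arms, yet adds that "use of a cluster-RCT design is recommended to in the future studies". Section 2.6 names one random effect, an intercept for repeated measures on the student. The article gives no ICC, design effect or class-level degrees of freedom.

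**The concern.** When classes are allocated, students in a class share a teacher, the delivery of the programme and an allocation. Section 2.1 says that one teacher covers all subjects, and that teacher also delivers the breaks. Two things then reduce power below that of an individually randomised trial of the same size: correlation between classmates inflates the variance of the arm difference, and the difference rests on five or six independent units, leaving 3 or 4 degrees of freedom. A calculation that treats 198 students as independent includes neither.

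The 80% claim supports the trial's primary hypotheses. If true power is well below it, a non-significant result could be read as evidence against the programme when the trial would probably have missed the planned effect. The recruitment forecast adds a smaller problem, because part of its range lies below the stated minimum.

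**Working it through.** **Inputs from the article.** f = 0.21, so d = 2f = 0.42 for two equal groups; alpha 0.05 two-sided; power 0.80; dropout 10%; total 198; five to six classes of 30 to 40; randomisation by class.

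**Assumed, because the article gives none.** ICC 0 to 0.10; pre-post correlation r of 0 (no baseline adjustment) to 0.9, taken to reduce the variance by the factor 1 − r² at both student and class level; equal class sizes; three classes per arm.

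**Step 1: reproduce 198.** For a two-group F test with noncentrality f²N and N − 2 denominator degrees of freedom, power is 0.798 at N = 179 and 0.8002 at N = 180. So N = 180, and 180 x 1.10 = 198. A normal approximation gives 89 per arm, 178 in total, and 178/0.9 = 197.8, again 198. Both routes assume independent students. Other variants do not give 198: a one-sided test gives 142 (158 with dropout), a repeated-measures interaction 91 or 47 (correlation 0 or 0.5), and a repeated-measures between-group test 136 to 172 (correlation 0.5 to 0.9).

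**Step 2: power with class as the unit.** With k = 3 classes per arm and m = 30 analysed per class (180 in all, the number the article's own calculation needs):

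SE = sqrt{ [ICC + (1 − ICC)/m] x (1 − r²) x (1/3 + 1/3) }, noncentrality = 0.42/SE, t on 6 − 2 = 4 df, two-sided critical value 2.776.

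Worked example, ICC 0.05 and r = 0: 0.05 + 0.95/30 = 0.0817; x 2/3 = 0.0544; SE = 0.233; noncentrality 1.80; power 28%.

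| ICC | Design effect 1 + 29 x ICC | r = 0 | r = 0.7 | r = 0.8 | r = 0.9 |
|---|---|---|---|---|---|
| 0 | 1.00 | 57% | 83% | 93% | >99% |
| 0.01 | 1.29 | 47% | 74% | 86% | 98% |
| 0.02 | 1.58 | 40% | 66% | 79.5% | 96% |
| 0.05 | 2.45 | 28% | 48% | 62% | 86% |
| 0.10 | 3.90 | 20% | 34% | 44% | 69% |

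The first row shows the cost of 4 df alone. At r = 0.7 the effect detectable with 80% power is d = 0.50, 0.63 and 0.79 at ICC 0.02, 0.05 and 0.10, against the planned 0.42. With five classes of 36 (3 df) and r = 0.7, power at those ICCs is 52%, 37% and 25%.

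**Step 3: leave out the degrees-of-freedom penalty.** By a normal approximation with 6 x 33 = 198 recruited, 178 analysed and no baseline adjustment, power is 80% at ICC 0, 70% at 0.01, 44% at 0.05 and 30% at 0.10. The shortfall is therefore not only a product of the 4 df.

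**Step 4: recruitment range.** 5 x 30 = 150, 5 x 40 = 200, 6 x 30 = 180, 6 x 40 = 240. Five classes need 198/5 = 39.6 students each; six need 198/6 = 33. Section 2.1 collects data only from consenting students and leaves out those with special health conditions or special education needs, so the usable number is lower than the class roll. At 150 recruited and 135 analysed, power is about 68% even with no clustering.

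**The case against.** **Baseline data may restore the power.** Section 2.6 analyses pre-test and post-test together, so the r = 0 column is pessimistic. With a strong correlation and a small ICC, 80% is reached: 86% at r = 0.8 and ICC 0.01, and 86% at r = 0.9 and ICC 0.05. With 40 analysed in each of six classes, r = 0.7 and ICC 0.01 give 82%. This stands. A reader might infer that the trial cannot detect the planned effect or cannot have 80% power; the documents do not support that, because they give neither ICC nor r. Equally, the article claims no gain from baseline data and gives no value on which 80% could rest.

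**The planned model is not a class-level t test.** The only random intercept that section 2.6 describes is for the student. If class were left out of the model, the first hazard would be false positives: a nominal 5% test would run at about 8%, 21% and 32% at ICC 0.01, 0.05 and 0.10 (29.7 analysed per class). This is a fair qualification. The power figures here describe an analysis that respects the randomisation. Power that came from omitting class would be bought with an inflated type I error, so it does not rescue the 80%.

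**The arithmetic of 198 is sound, and the class range contains 198.** Both are true. The fault lies in the independence assumption. The class count is a forecast straddling a stated minimum, so it is a secondary shortfall and not a contradiction.

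**The limitation may mean randomising schools.** The cluster sentence follows a remark on contamination, and section 3.1 is open about class randomisation and about one teacher's influence when classes are few. That reading is possible. As worded, however, it implies that the present trial is not cluster-randomised.

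**Conclusion.** The point holds. The 198 is an individual-level calculation applied to a trial that randomises five to six classes, so 80% power at f = 0.21 is unsupported and probably too high. With six classes of 30 analysed and inference on 4 df, power over ICC 0.01 to 0.10 runs from 47% down to 20% without baseline adjustment, and from 74% down to 34% at r = 0.7. At that size, a positive ICC is compatible with 80% only when it is small and the pre-post correlation is strong. These figures rest on assumed ICC and r, equal class sizes and a 3:3 split. That the calculation omits clustering does not depend on them.

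The recruitment shortfall is secondary: the lower part of the 150 to 240 range misses 198 before non-consent and exclusions. It would also be wrong to conclude that the trial is sized for a large effect. The detectable values at r = 0.7 are 0.50 to 0.79 over ICC 0.02 to 0.10, and section 2.6 takes 0.5 as medium and 0.8 as large.

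**What to change.** 1. In section 2.1, withdraw the claim of 80% power at f = 0.21, or replace it with power and detectable effect computed with class as the unit. Use declared ranges of ICC (for example 0.01 to 0.10) and pre-post correlation (for example 0.5 to 0.9), and give the degrees of freedom. Do not describe the trial as sized for a large effect.
2. State that the plan reaches 198 only with six classes of at least 33 consenting, eligible students, or five classes of about 40.
3. Reword section 3.1 to acknowledge that this trial is itself cluster-randomised by class. If the recommendation for future studies concerns randomising whole schools, say so.

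The cost is a change of wording and a less favourable stated power. No enrolment beyond the stated 198 is required.

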#### Control group

2.2.3

The classes that will be randomized in relation to the control group will not receive the IcPAB within 12 weeks of the intervention. However, those schools will be given all the resources to implement IcPAB activities once the post-test data collection is fulfilled. During the intervention period, the control group’s teachers will be contacted once weekly through WhatsApp phone calls by the principal investigator and twice a week physically by the principal investigator/ research assistants. Correspondence will be maintained to obtain information about their lesson delivery patterns to ensure that the control group did not receive interventions to change their normal study modes.

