### Fidelity of the intervention

2.4

The primary source for assessing the fidelity will be the logbooks of the teachers. An example of a log sheet can be found in Supplementary material S6. Teachers will indicate how many IcPAB they implemented daily throughout the intervention period. Teachers will be reminded every day via WhatsApp messages to carry out IcPAB, and a research team member will visit the schools once a week to check if the logbooks are duly filled. The personal visits to the intervention schools will also minimize issues with time management and PA breaks implementation from the teachers’ side. In addition, accelerometer data from the post-test will be compared with the responses obtained through teacher and student interviews at the post-test.

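### Five to six classes from two schools are block-randomised without stating that blocking is within school, the model names no school term, and the text conflicts on whether one school can hold both arms

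*Protocol article*

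**What the plan says.** Section 2.1 sets the scale of the trial: "it is anticipated to recruit five to six classes (30 to 40 students per class) from two government schools". It then gives the allocation method: "Block randomization technique via MS Excel, will be used to randomize the sample classes by an assessor who is blinded" to intervention content and outcome assessment. Block size, block composition, stratification by school and the number of classes in each school are not given.

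Section 2.6 fits a generalised linear mixed model over pre-test and post-test, with a random intercept for the repeated measures on each child. It names no school term.

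On whether a school can contain both arms, the text points two ways:

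- **Classes are the unit.** Section 2.1 randomises classes and speaks of intervention classes. Section 2.2.3 opens with randomised classes. Section 3.1 warns of contamination because classes are randomised, which presupposes both arms in the same school.
- **Schools are the unit.** Section 2.2.3 goes on to say of the control condition that "those schools will be given all the resources to implement IcPAB activities once the post-test data collection is fulfilled". Section 2.4 says: "The personal visits to the intervention schools will also minimize issues with time management".

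**The concern.** With two schools and at most six classes, the allocation can easily put most or all of one arm in one school. The group-by-time estimate would then carry whatever differs between the schools over the 12 weeks. The article itself describes three such sources:

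- Extra classes for the scholarship examination are held according to each school's interests (section 2.1). They bear directly on the primary outcomes, mathematics and reading.
- Reading is scored by a teacher from a parallel class in the same school (section 2.3.1.2), so raters differ by school.
- Sudden school closures are expected (section 3.1) and need not be the same in both schools.

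If arm and school coincide completely, no analysis can separate them. Section 3.1 lists contamination and the small number of classes as limitations, but not this.

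**Working it through.** **The plan's own figure.** Inputs from sections 2.1 and 2.6: f = 0.21, so d = 2f = 0.42; power 0.80; alpha 0.05, two-sided ("A 5% level (two-tailed) will be used as the statistical significance cut-off point"); sample size set "with an estimated 10% dropout rate". The two-group formula n = 2(1.96 + 0.842)²/0.42² gives 89 per arm, 178 in total, and 178/0.9 = 198. The exact F test gives 180, and 180 × 1.1 = 198. The stated 198 reproduces, so the sample size arithmetic is not in question here.

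**Allocation check.** Assumptions, since the article gives none of these: the split of classes between schools; 3 classes per arm out of six, or 2 against 3 out of five; and one block that ignores school. With s₁ and s₂ classes in the schools and t treated classes, the number of allocations with x treated classes in school 1 is C(s₁, x) × C(s₂, t − x), out of C(s₁ + s₂, t).

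The arm–school correlation is (ad − bc)/√[(a+b)(c+d)(a+c)(b+d)]. Here a and b are the treated and control classes in school 1, and c and d those in school 2. Example, 4+2 with three treated in the larger school: (3×2 − 1×0)/√(4×2×3×3) = 6/8.49 = 0.71.

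| Split | Arm = school | Other allocations (absolute correlation) |
|---|---|---|
| 3+3 | 2 of 20 (10%) | 18 of 20 are 2:1 splits (0.33) |
| 4+2 | impossible | 8 of 20 (40%) put both classes of the smaller school in one arm (0.71); 12 of 20 balanced (0) |
| 5+1 | impossible | all 20 unbalanced (0.45) |
| 3+2 | 1 of 10 (10%) | 3 of 10 (0.67); 6 of 10 (0.17) |
| 4+1 | impossible | all 10 unbalanced (0.41 or 0.61) |

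**Effect on the estimate.** Let δ be the difference between the schools in 12-week change that has nothing to do with the intervention. With classes of equal size, the unadjusted group-by-time contrast is shifted by δ times the difference between arms in the share of classes from school 1. That multiplier is:

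- 1 when arm and school coincide;
- 0.67 for the lopsided 4+2 allocations;
- 0.33 for 2:1 splits in 3+3;
- 0 for balanced 4+2.

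A constant difference in level between schools appears at both time points and drops out.

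**With allocation inside each school.** For 4+2 the result is 2:2 and 1:1, correlation 0. For 3+3 each school still splits 2:1 or 1:2, so the correlation is 0.33 if the splits are reversed between schools and 0 if they run the same way (4:2 overall). For 3+2 it is 0.17. Complete confounding cannot occur when each school has at least two classes.

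**The case against.** The article is silent on what forms a block. A reader might infer that the randomisation ignores school, but the text does not say so, and a condensed article may leave block composition to the full protocol. The participant flowchart and the supplementary SPIRIT checklist could not be seen for this check. Blocks of two run down a list sorted by school would rule out complete confounding for 3+3 and 4+2. This stands, and the percentages above are therefore conditional.

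A reader might also infer that whole schools are the arms. The wording in sections 2.2.3 and 2.4 allows it, but it can also mean schools that contain control or intervention classes, and the contamination remark in section 3.1 speaks against it. What stands is a conflict in the text, not evidence of whole-school allocation.

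The third objection is that the pre/post contrast removes fixed differences between schools in attainment, facilities or stress. That is largely right and narrows the harm to differing trends. It also means that a school main effect would be no remedy: in a linear random-intercept model with complete pre and post data, a term constant over time leaves the group-by-time estimate unchanged.

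The objection does not dispose of the three school-level influences that the article itself describes, nor of the contradictory wording.

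**Conclusion.** The point holds in a limited form. Neither the allocation nor the model, as described, protects against arm–school imbalance, and the sections disagree on whether a school can contain both arms. With a single block that ignores school, complete confounding has a 10% chance for an assumed 3+3 or 3+2 split and is impossible for 4+2, 5+1 or 4+1. Some imbalance arises in 40% of allocations for 4+2 and in all of them for the other splits, though it is slight (0.17) in most 3+2 allocations. If the school wording is literal, confounding is complete. The bias is confined mainly to school-specific trends over the 12 weeks, and the documents give no figure for their size. It would go too far to say that school is known to be ignored or that the trial has one school per arm. Because the remedy is nearly free and the relevant trends are described in the article, the change should be made.

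**What to change.** 1. Allocate classes separately within each school, so that every school with at least two classes contains both arms, and say so in section 2.1. A 4+2 split is then exactly balanced. A 3+3 split keeps 2:1 divisions but cannot be fully confounded. A school with a single class cannot hold both arms, so 5+1 and 4+1 remain unbalanced.
2. State the number of classes per school.
3. Add school and school-by-time as fixed effects in section 2.6. The interaction is the term that adjusts the group-by-time estimate.
4. Reconcile sections 2.2.3 and 2.4 with class-level allocation, referring to classes rather than schools where classes are meant.

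If allocation is already done, report it by school and add the school-by-time term. If arm and school turn out to coincide, that term cannot be separated from the treatment effect, and the report must say so.

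Cost: a changed allocation list and one degree of freedom. Counted at class level, six classes in two arms leave 6 − 2 = 4 degrees of freedom, which falls to 3 with school; five classes go from 3 to 2. With so few classes that loss is noticeable.
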